## Background

Lung cancer accounts for a fifth of the total global burden of disability-adjusted life years due to cancer [1]. Non-small cell lung cancer (NSCLC) is the most prevalent type of all lung cancers [1], with surgical resection appearing to be the most effective treatment in early stages (Stages I and II) [2].

Although surgical resection results in higher survival rates [3], it is associated with significant morbidity, functional limitations and decreased quality of life (QoL) [4].

Long-term physical impairment is an important and undesirable consequence of surgery, limiting patients’ recovery to a greater extent than do other severe pulmonary complications, such as atelectasis, dyspnoea and pneumonia [2, 5]. Furthermore, chronic obstructive pulmonary disease (COPD) is frequent in lung cancer patients and is associated with increased postoperative morbidity and mortality [6–8].

Recent studies suggest that perioperative pulmonary rehabilitation (PR) programmes including exercise may improve exercise capacity, functional performance and QoL, both pre- and postoperatively [2, 9].

PR is a comprehensive intervention that includes exercise training (endurance and resistance), education and behaviour changes [10, 11]. PR is also part of the new integrated pathways for enhanced recovery, where it has shown to improve patient satisfaction and to reduce in-hospital stay [12].

Surgical candidates seem to benefit from preoperative PR. In COPD patients, preoperative PR is correlated with improvement in functional parameters, which in turn may increase resection rate and allow more extensive lung resections [3, 10].

It is well known that exercise training is associated with significant increase in peak oxygen consumption (VO2peak) [13–15], which has been confirmed as a strong independent predictor of perioperative or postoperative complications and overall long-term survival for individuals with NSCLC [11, 16]. Indeed, patients with reduced exercise tolerance and low VO2peak show poorer thoracic surgical outcomes [11, 16]. Therefore, preoperative PR could reduce symptoms and morbidity, shorten hospital stay and lower healthcare costs [17, 18].

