### Additional assessments

Data regarding patient compliance and treatment-related side effects during both preoperative and postoperative intensive PR will also be collected.

Intensive PR includes the implementation of hospital-based and home-based training. Patients randomized to the treatment group are requested to register the activities performed at home on a training log; distance in kilometres, number of steps and heart rate achieved during aerobic walking and exercises performed during respiratory muscle training (RMT) session are recorded. As patient adherence to protocol is a crucial issue in rehabilitation and the literature recommends the consistent and explicit reporting of exercise attendance in people with respiratory diseases [24], the proportion of training sessions performed are collected to assess patient compliance: adherence to the protocol is defined as the achievement of 80% or more of the training exercises prescribed [25].

We consider as minor side effects self-reported pain or discomfort in the muscles/joints involved with the physical component of the treatment; major side effects include any trauma secondary to a fall requiring specific interventions or symptomatic alterations of the basic vital signs (i.e., blood pressure, heart rate) arising during or shortly after the end of exercise and confirmed by instrumental measurement.

To evaluate the actual effect of lung resection on the study population before the postoperative treatment, FEV1, FVC and DLCO are also registered in the experimental group one month after surgery and compared to baseline.

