## Methods

### Study design

A single institution 1:1 randomized controlled open-label trial with two parallel arms, powered for superiority, has been designed in accordance with the CONSORT statement and Helsinki declaration. The study has been approved by the local Ethical committee [n. 2013/0009390] and funded by the Italian Ministry of Health [GR-2011-02351711].

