### Participants and setting

All patients with highly suspicious or diagnosed primary NSCLC are screened for eligibility criteria within the Lung Cancer Multi-Disciplinary Team Meeting at Arcispedale Santa Maria Nuova (ASMN) of Reggio Emilia, Italy. This is an Institute for Advanced Technologies and Healthcare Protocols in Oncological Research certified by the Organization of European Cancer Institutes in 2014. The Thoracic Surgery Unit’s catchment area covers a range of about 535,000 inhabitants and performs an average of 500 operations per year, including about 130 lung resections for malignancies.

Patients with Stages I and II NSCLC are considered for enrolment if they qualify for surgery. We exclude candidates who require adjuvant therapies and patients unfit for the physical exercise required by intervention [Table 1]. In patients affected by COPD, medical treatment is reviewed and optimized according to the most recent Global Initiative for Chronic Obstructive Lung Disease guidelines at the start of the selection process, to minimize confounding factors.

**Table 1 Tab1:** Inclusion and exclusion criteria

Inclusion criteria	Exclusion criteria
Patients affected by NSCLC in Stage I-II	Tumour stage requiring adjuvant therapies
Patients eligible for lung resection	Patients unfit for the type of physical exercise included in study protocol
Patients able to walk autonomously without medical devices (e.g., crutches)	Patients affected by sensorial or cognitive deficits with potential severe impact on compliance (deafness, blindness, dementia, etc.)
Patients able to give informed consent	

Written informed consent is obtained from participants by the operating surgeon during the preoperative consultation. Subsequently, patients undergo baseline assessment and afterwards are randomized to receive intensive PR (Intervention Group - IG) or SC (Control Group - CG) (Fig. 1).

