### Statistical considerations

#### Sample size

Since data for mean and standard deviations of 6MWT after lung surgery with or without treatment have never been published, Cohen’s medium effect size (d = 0.5) has been used to compute sample size based on the minimal significant variation reported (25 m) [33].

We also expect a potential dropout rate of about 10% for the aforementioned reasons. Thus, assuming 5% type I error and 80% power for this study, we plan to enrol 140 patients (about 70 patients in each arm).

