#### Statistical analysis

Statistical analyses will be performed according to the intention-to-treat approach. Statistical techniques per study aims are as follows:
*Primary aim:* t-test for independent samples to compare the mean of the change (defined as T3 – T0 related date) in 6MWD between IG and CG. In case of heteroscedasticity, checked by folded F test, the Satterthwaite adjustment will be used.
*Secondary aims*:- t-test for independent samples to compare the mean of the change between IG and CG for 6MWD (T2 – T0 change), FEV1, FVC, DLCO and SF-12 score (T3 – T0 change), HADS score (T1 - T0 and T3 - T0), NRS score (T2 – T0 and T3 – T0) and LoS. In case of heteroscedasticity, checked by folded F test, the Satterthwaite adjustment will be used.- chi-square test to compare the proportion of postoperative complications between IG and CG;

Five percent significance will be used to assess the *p*-values and 95% two-sided confidence interval will be provided for each tested parameter; the confidence intervals will be calculated assuming normal distribution.

Statistical calculations will be performed by the local Research and Statistics Unit using SAS System release 9.2 or later, R release 3.3.3 or later, SPSS release 23 or later, according to the availability at the time of the data analysis.

Patient adherence to protocol may be a crucial issue in determining the efficacy of rehabilitation programmes, including exercise training. Although it has not been plainly demonstrated, in principle, non-attendance could affect exercise dose and influence the outcome of treatment [34]. Therefore, if patient compliance, is less than 80% [25], we will proceed with a second per-protocol analysis.

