In addition, because preoperative diagnosis may not always be obtained and, whenever possible, it seems to be a significant barrier to trial enrolment [42], we chose to include patients without proven cancer histology, providing that the clinical evaluation is consistent with malignancy (PET positivity, history of smoking, radiological features of malignancy, absence of concomitant extra-thoracic malignancies).

The exclusion of patients undergoing adjuvant therapies might represent a limit of this study, because it leads to a further selection of patients that could impact reproducibility in the future. However, in patients with lung cancer little is known about feasibility of physical exercise during chemo or radiotherapy, whose side effects might offset the potential benefits of PR. Thus, we chose to sacrifice broader inclusion criteria to find reliable answers, first and foremost, in the population that could most benefit from PR.

We emphasize the need for a timely delivery of preoperative PR to comply with the regional guidelines, which recommend starting cancer treatments within 30 days from referral [32]. If the results of this study show a clear benefit of intensive PR in patients with lung cancer, especially in improving QoL, a future trial on combined PR and non-radical treatments to extend the benefit of improved functioning to patients with advanced disease may be warranted. Likewise, the use of preoperative PR, if beneficial, will need to be evaluated in patients with severe COPD to increase the rate of lung resection.

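### The covariate-free t-test on six-month change in FEV1, FVC and DLCO is valid but less precise than it could be: it uses neither the baseline value as a covariate nor the extent of resection planned before randomisation.

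*Protocol article*

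**What the plan says.** Under Secondary aims in the Statistical analysis section, the change from T0 to T3 in "FEV1, FVC, DLCO and SF-12 score" is compared between arms by a t-test for independent samples, with the Satterthwaite adjustment if the folded F test shows unequal variances. No covariate is named. The same section states: "Statistical analyses will be performed according to the intention-to-treat approach". The Study design section describes "A single institution 1:1 randomized controlled open-label trial".

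Table 1 admits "Patients eligible for lung resection" and sets no limit on how much lung is to be removed. The Background, citing literature on COPD patients, links preoperative rehabilitation to better functional parameters, "which in turn may increase resection rate and allow more extensive lung resections".

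Under Additional assessments the protocol aims to gauge the effect of the resection itself: "FEV1, FVC and DLCO are also registered in the experimental group one month after surgery and compared to baseline". The control group has no such measurement.

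**The concern.** Six-month lung function after resection reflects, to a large degree, the patient's starting value and the amount of lung taken out. Operations of any extent are admitted, so the change scores will vary between patients for a reason unrelated to rehabilitation. A two-sample t-test on change leaves all of that variation in the error term. Subtracting the baseline does not solve this. If the loss is roughly a fraction of the starting value, patients who start higher lose more in absolute terms, so the change still depends on the baseline.

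At stake are the width of the confidence intervals for three secondary outcomes and how a reader interprets them. The Background says that evidence for meaningful lung-function change after postoperative rehabilitation is insufficient, and the sample size was not set for these outcomes, so precision is worth having. The one-month lung function tests do not fill the gap, because a measurement in one arm cannot separate surgery from rehabilitation in a comparison between arms.

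**Working it through.** **1. The plan's own figure.** Inputs from the Sample size section: standardised difference 0.5 (25 m, hence SD 50 m), 5% type I error taken as two-sided, 80% power, 10% dropout.

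n per arm = 2 × (1.96 + 0.8416)² / 0.5² = 2 × 7.849 / 0.25 = 62.8, rounded up to 63. The total is 126, and 126 / 0.90 = 140. This reproduces "assuming 5% type I error and 80% power for this study, we plan to enrol 140 patients". The figure concerns walking distance only; no power is stated for lung function. About 63 per arm is the number expected to be analysed.

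**2. Is the t-test valid?** The t-test was simulated with 63 per arm, 20,000 runs per scenario and no direct effect of rehabilitation on lung function. Assumed, not in the documents: 15% of control patients have a larger resection, which costs an extra 0.5 to 1.5 SD.

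| Larger resections, intervention vs control | Expected difference (SD, against intervention) | Rejection rate |
|---|---|---|
| 15% vs 15% | 0 | 5.0–5.3% |
| 20% vs 15% | 0.025–0.075 | 5.2–6.6% |
| 25% vs 15% | 0.05–0.15 | 5.9–10.8% |
| 30% vs 15% | 0.075–0.225 | 7.1–18.9% |

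The expected difference is the extra loss times the difference in shares, for example 1.5 × 0.15 = 0.225. In the first row the test holds its 5% level. In the other rows it detects a real total effect that runs through the operation. That is not a false positive for the strategy, but it could not be read as a direct effect on the lung.

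**3. How much variance could be explained?** All inputs here are assumptions: 19 segments; baseline FEV1 2.2 L (SD 0.6); 20–35% sublobar, 60–75% lobectomy, 5–10% larger; loss = baseline × segments/19 × a factor of 0.6 to 0.9, plus residual SD 0.2–0.3 L; 10% of operations differ from plan.

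- R² for the change with the baseline value alone: 0.04–0.14.
- R² with baseline and planned segments: 0.14–0.46.
- Residual variance of the second model relative to the first: 0.62–0.90, so planned extent removes a further 10–38%.
- Interval width: √0.90 = 0.95 and √0.62 = 0.79, so about 5–21% narrower.
- Equivalent sample size: 1/0.90 = 1.11 and 1/0.62 = 1.61, so like roughly 11–60% more patients for these outcomes.
- Against the planned t-test on change, which has no covariates, the residual variance is 1 − R² = 0.86 to 0.54, so baseline and planned extent together remove about 14–46%.

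A cruder two-class version gives a similar picture. With 15% larger resections costing D SD, the share explained is v/(1 + v) with v = D² × 0.15 × 0.85. That is 0.03 for D = 0.5 and 0.22 for D = 1.5.

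**4. Chance imbalance in litres.** With an assumed SD of 1.7 segments, the standard error of the between-arm difference in mean extent is 1.7 × √(2/63) = 0.30 segments. One segment is 2.2/19 = 0.116 L if loss is fully proportional. With the factors of 0.6 to 0.9 it is 0.07–0.10 L, so 0.30 segments is about 0.02–0.03 L. This component is already inside the t-test's standard error; the adjusted model removes most of it.

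**The case against.** The strongest case against is that nothing is wrong with the test. In a randomised intention-to-treat comparison, leaving out a prognostic variable does not bias the difference between arms, and the confidence interval already allows for chance imbalance. That stands in full.

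Three stronger readings are tempting, and the documents support none of them.

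- A reader might infer that a chance difference in extent makes the t-test biased. It does not; the cost is precision only.
- A reader might infer that the protocol expects rehabilitation to enlarge resections in this trial. The Background sentence is hedged literature about COPD patients. COPD patients can enter, so the pathway cannot be ruled out. But everyone enrolled is already a candidate for resection, and the Discussion leaves the related question to later work: preoperative rehabilitation "will need to be evaluated in patients with severe COPD to increase the rate of lung resection".
- A reader might infer that adjusting for planned extent would remove a treatment-driven change in the operation. It cannot, because planned extent is fixed before treatment. Actual extent arises after randomisation, and conditioning on it answers a different question and may itself introduce bias.

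It is also fair to say that a condensed article may leave operative data fields and supportive analyses to documents not shown. The absence of extent from Table 2 is therefore not held against the plan. What remains is that the article does fix a specific covariate-free test for these outcomes, and a more precise one is available at little cost.

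**Conclusion.** The point holds as one of precision and interpretation for secondary outcomes. The t-test on change in FEV1, FVC and DLCO validly estimates the total effect of the strategy, but it leaves out two predictors that can be fixed before randomisation.

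The size is uncertain. About 10–38% less residual variance from planned extent, beyond the baseline value, rests wholly on assumed resection mixes, losses and residual SDs for FEV1. Nothing was calculated for FVC or DLCO. If nearly all patients have the same type of operation, or plans often change in theatre, the gain would be at or below the lower end. That planned extent is known before randomisation is itself an assumption. It is plausible, since the operating surgeon takes consent and preoperative rehabilitation starts at or just after listing for surgery, but the article does not state it.

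**What to change.** - Analyse T3 FEV1, FVC and DLCO each by a linear model with arm, the T0 value and the extent of resection planned before randomisation (for example, number of segments). Report the adjusted difference with its 95% confidence interval. The unadjusted t-test may be kept as a sensitivity analysis.
- Take planned extent only from records made before randomisation. For patients already enrolled, use it only where such a record exists.
- Report the resection actually performed by arm, so that readers can judge whether any total effect could run through the amount of lung removed.
- Do not put actual extent in the main model. Label any analysis that uses it, such as a comparison with predicted postoperative values, as supportive and conditional on a post-randomisation variable.

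The cost is one data field, if it is not already collected, some retrieval from surgical listings, and a few lines of analysis text. Two extra model terms cost almost nothing with about 126 patients analysed.

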#### Duration and timeline

The study started enrolling in 2015. Results are expected by the end of 2017.

## Discussion

The main aim of PuReAIR is to assess the effectiveness of intensive combined pre- and postoperative PR in improving exercise capacity, lung function and long-term outcomes (QoL, pain, anxiety and depression) in lung cancer patients surgically treated with curative intent.

So far, the long-term effect of physical therapy on exercise tolerance and quality of life has only been reported in small series, and recent reviews have highlighted the need for well-designed studies to collect stronger evidence and clarify the role of perioperative PR [2, 5, 23].

The RCT design adopted allows reducing possible sources of bias (selection bias) and confounding factors which could be embedded in the heterogeneity of the target population. Moreover, this study design was powered according to an a priori specified hypothesis of superiority of intensive PR compared to SC.

The intervention of any trial should always be based on the best available evidence and described in sufficient detail to be reproducible. The study protocol provides a detailed description of the interventions delivered; this is particularly important in trials focusing on complex interventions, as is the case in rehabilitation. In fact, a comprehensive description of both standard care and additional treatments allows an accurate interpretation of the conclusions and ensures the correct replication of the protocol described, if appropriate, in order to compare results.

The definition of the best PR treatment programme required a careful review of the current literature [23], resulting in the definition of the following key elements:The inclusion of both aerobic and strength training of lower and upper limb muscles [2, 11, 35];The combination of outpatient and home-based treatment sessions. This should facilitate the enrolment of patients referred from provincial hospitals and might increase their compliance, minimizing the risk of attrition bias;The inclusion of inspiratory muscle training, incentive spirometry, airway clearance techniques and/or respiratory exercises, as lung cancer leads to respiratory impairment and COPD is a frequent comorbidity in patients affected by lung cancer [19, 20, 36, 37];The inclusion of group exercise training sessions during the postoperative phase, alongside individual guided and monitored home-based training, to facilitate mutual support among patients with NSCLC, whose vulnerable psychosocial condition could affect postoperative functioning and QoL [38]. In fact, a recent systematic review examining the spectrum of health care needs among people with lung cancer showed that psychological, emotional and social needs were most frequently specified and lack of acknowledgement of patients’ status by others were perceived as important issues [39]. Therefore, group sessions may facilitate the sharing of feelings, experiences and concerns, and may support patients in coping with their illness;The inclusion of scar massage in the postoperative phase to relieve tissue tension and reduce pain. In our clinical experience, patients frequently report pain and hypersensitivity around surgical scar.

At the time of planning this protocol, we estimated an overall 10% withdrawal rate, mainly due to perioperative morbidity and mortality, as well as unforeseen N1/N2 lymph nodal involvement diagnosed after surgery and requiring adjuvant therapies. However, more recent literature suggests a greater incidence of intraoperative lymph nodal upstaging [40] and even when an accurate staging workup is performed, including PET/CT and EBUS-TBNA when appropriate, minimal involvement of hilar nodes (N1 stage) remains difficult to assess preoperatively. Furthermore, more aggressive protocols are recommended by international guidelines in treating N1 NSCLC [41]. A greater than expected number of patients may therefore withdraw post randomization to ensure they receive the best cancer care.

In addition, because preoperative diagnosis may not always be obtained and, whenever possible, it seems to be a significant barrier to trial enrolment [42], we chose to include patients without proven cancer histology, providing that the clinical evaluation is consistent with malignancy (PET positivity, history of smoking, radiological features of malignancy, absence of concomitant extra-thoracic malignancies).

The exclusion of patients undergoing adjuvant therapies might represent a limit of this study, because it leads to a further selection of patients that could impact reproducibility in the future. However, in patients with lung cancer little is known about feasibility of physical exercise during chemo or radiotherapy, whose side effects might offset the potential benefits of PR. Thus, we chose to sacrifice broader inclusion criteria to find reliable answers, first and foremost, in the population that could most benefit from PR.

We emphasize the need for a timely delivery of preoperative PR to comply with the regional guidelines, which recommend starting cancer treatments within 30 days from referral [32]. If the results of this study show a clear benefit of intensive PR in patients with lung cancer, especially in improving QoL, a future trial on combined PR and non-radical treatments to extend the benefit of improved functioning to patients with advanced disease may be warranted. Likewise, the use of preoperative PR, if beneficial, will need to be evaluated in patients with severe COPD to increase the rate of lung resection.

